### Recruitment and Follow-Up

A trained researcher identified all eligible patients, evaluating inclusion and exclusion criteria, by checking the patient’s health records stored in the electronic database of the hospital. Successively, during the first clinical consultation, the investigator briefly introduced the study to each eligible patient and collected informed consent from those interested in participating. During this first meeting, the investigator gave a short training in Noona and created the patient account. The investigator could use Noona to monitor the response status of questionnaires for each patient and could contact them to stimulate adherence to the study, completion of the questionnaires, and support for any issues with the platform.

### Statistical Procedures

#### Statistical Considerations on the Design

Data collected by Noona are stored centrally by the Foundation for Research and Technology–Hellas (FORTH); the data will be cleaned, homogenized, and shared with the Institute of Communications and Computer Systems (ICCS) for joint conduction of analyses. Interim analyses and quality checks will be conducted on data extracted at different time points during the project (eg, after the month 6 data are complete). Descriptive statistics (ie, mean, SD, median, maximum and minimum, and graphical representation) will be used to summarize the continuous data. Discrete measures will be summarized using counts, percentages, and graphical representations. Bivariate charts will be produced whenever desired. Temporal data mining, time-series prediction, sequence classification methods, clustering time-series data, and temporal association rules will be used to develop and validate the predictive model. Mediation, moderation, and moderated mediation analyses have a central role in the statistical methodology. In order to investigate whether the modality of data collection (ie, paper and pencil or the eHealth platform, Noona) will affect results on self-reported outcomes, analysis will be performed stratifying patients based on the method used to respond. Similarly, patients will be stratified based on sociodemographic (eg, country) and clinical variables (eg, cancer stage).

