**Methods:**

A total of 660 women with breast cancer will be recruited from five European cancer centers in Italy, Finland, Israel, and Portugal. Biomedical and psychosocial variables will be collected using the Noona Healthcare platform. Psychosocial, sociodemographic, lifestyle, and clinical variables will be measured every 3 months, starting from presurgery assessment (ie, baseline) to 18 months after surgery. Temporal data mining, time-series prediction, sequence classification methods, clustering time-series data, and temporal association rules will be used to develop the predictive model.

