### Objectives

The primary objective of this multicenter clinical pilot study is to identify the interplay of clinical, biomedical, and psychosocial factors in predicting patients’ resilience to breast cancer at several time points after diagnosis.

The secondary objectives are as follows:

Differentiating between trajectories of psychological adaptation to breast cancer.Developing a multidimensional index of resilience as a function of biomedical status, psychosocial status, and functional status.Examining potential differences in the predictive and outcome variables across the four clinical sites in which the study is conducted.Cross-validating the prediction models in order to assess the accuracy of their performance in practice and to enhance their generalization.

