## Methods

### Study Design and Clinical Partners

The clinical pilot study has been designed as a longitudinal prospective cohort, with assessments at diagnosis of breast cancer and 3, 6, 9, 12, 15, and 18 months later. It involves different clinical centers in several countries, namely the European Institute of Oncology (IEO) in Italy, Helsinki University Hospital (HUS) in Finland, the Champalimaud Clinical Centre (CHAMP) in Portugal, and the Rabin and Shaare Zedek Medical Centers, coordinated by the Hebrew University of Jerusalem (HUJI) in Israel. Data were primarily collected through the Noona Healthcare platform (Noona), a personal health records system designed for patients with cancer. For those patients who do not want or are unable to use Noona, the paper-and-pencil mode are available. Data are then inserted into the Noona platform by a researcher. Noona is a fully responsive web application that is usable with a web browser on any suitable device that is available to the user, including desktop, laptop, tablet, and smartphone devices. Noona is classified as a medical device; more specifically, it is classified as a web platform designed for patients with cancer for remote monitoring and as a support tool for communication between patients with cancer and health care professionals. However, in the multicenter clinical study, Noona will not be used for communication between the treatment team and patients, but will only be used for the collection of study-relevant information. Thus, the main functionalities, such as reporting symptoms or requesting assistance, will not be taken into consideration. The study was registered at ClinicalTrials.gov (NCT05095675).

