### Study Participants

Women with histologically confirmed stage I to III breast cancer have been recruited across the several study centers, with 660 patients recruited at baseline. Details on the inclusion and exclusion criteria are provided in the Selection Criteria section below.

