#### Sample Size Considerations

In the context of conventional statistical approaches, such as multiple linear regression, that have typically been employed in the existing relevant literature, a minimal sample size (n=500, considering maximal attrition rates of approximately 40%) is sufficient to ensure 85% power at *P*<.05; this will allow detection of the cumulative contribution of up to 30 independent predictors accounting for as little as 5.3% of total variance of each key study outcome. Furthermore, in a regression model with 30 independent variables, this sample size is sufficient to detect the significant added value of each independent variable, assuming a small effect size (Cohen *f*^2^>0.018). It should be noted, however, that this study proposed, for the first time, the use of nonconventional computational approaches to assess the hypothesized predictive variables. Given the complexity of the data sets and the fact that interactions between parameters are often difficult to specify—a requirement of conventional methods—supervised machine learning methods are emerging as the approach of choice for identifying hidden patterns among predictor variables. Perhaps the most distinct advantage of these methods is their adaptive capacity (ie, their inherent ability to optimize parameter weights based on known individual outcomes). The clinical accuracy of each optimized prediction model will be tested through various cross-validation techniques. 

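### Stratifying by response mode cannot show whether paper or Noona affects the answers, because patients select their own mode

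*Protocol article*

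**What the plan says.** In the Protocol article, the section Statistical Considerations on the Design poses a question, whether the mode of data collection changes the results on self-reported outcomes, and names one method to answer it: "analysis will be performed stratifying patients based on the method used to respond". The next sentence extends the method to other factors: "patients will be stratified based on sociodemographic (eg, country) and clinical variables (eg, cancer stage").

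Study Design and Clinical Partners explains how a woman comes to answer on paper: "For those patients who do not want or are unable to use Noona, the paper-and-pencil mode are available".

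The power statement is under Sample Size Considerations. It rests on "a minimal sample size (n=500, considering maximal attrition rates of approximately 40" per cent) and gives "85% power at *P*<.05" for a regression with up to 30 predictors. It mentions no subgroup by mode, country or stage.

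**The concern.** Mode is chosen by the patient or forced on her by ability. A woman who cannot or will not use a web application may differ from one who does in ways that bear on anxiety, distress, quality of life or resilience scores. Splitting the sample by mode leaves those differences in place. If the paper stratum scores worse, the cause may be the paper form or the women who use it. If the strata agree, a real mode effect may be cancelled by an opposite difference in case mix.

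The risk is a wrong methodological conclusion. A mode effect could be claimed and paper data discounted, or mode could be declared harmless and the data merged without adjustment. Either choice would carry into the prediction models built on the merged data.

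For country and stage the issue is different. Results shown stratum by stratum do not in themselves test a difference between strata, and the planned power does not extend to them.

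**Working it through.** **1. The mode comparison.** Write *d* for the effect of answering on paper rather than on Noona, and *s* for the difference in mean outcome that the two groups of women would show if all used the same mode. Comparing the strata estimates

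mean(paper) − mean(Noona) = *d* + *s*.

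Stratification gives one equation for two unknowns. It isolates *d* only if *s* = 0, which random assignment of mode would give in expectation. Here mode follows willingness and ability, so nothing in the design makes *s* zero. Adjustment removes the part of *s* explained by measured baseline variables. Year of birth and level of education are collected at month 0 (Table 2), and centre and country are known for every woman.

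The article does not state how many women use paper. If the share were 5% to 30% (an assumption), the paper group would be:

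- 25 to 150 of 500 women;
- 33 to 198 of the 660 recruited;
- 20 to 119 of the 396 left after 40% attrition (660 × 0.60).

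At the lower end, a separate paper stratum could support little beyond description.

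**2. The plan's own power figure.** Inputs from Sample Size Considerations: n = 500, 30 predictors, R² = 5.3%, single-predictor f² = 0.018, alpha 0.05. Method: noncentral F with noncentrality f² × n and error df n − 31 = 469.

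- All 30 predictors: f² = 0.053 / 0.947 = 0.056; power 84.4%.
- One predictor: f² = 0.018; power 84.9%.

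The stated 85% reproduces to rounding for the whole sample.

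**3. What that figure does not cover.** As an illustration only, assume an equal split over four countries and the same 30-predictor model within each. The article states neither. Nor is it clear whether 500 is before or after attrition, so four readings are shown.

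| Reading | Women per country | Power, one predictor at f² = 0.018 |
|---|---|---|
| 500 × 0.60 / 4 | 75 | 20.6% |
| 660 × 0.60 / 4 | 99 | 26.0% |
| 500 / 4 | 125 | 31.8% |
| 660 / 4 | 165 | 40.2% |

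On every reading the 85% cannot be carried over to a country stratum.

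**4. How many interactions a pooled model can bear.** Four countries use 3 df, three stages 2 df and two modes 1 df. Crossing all 30 predictors with all three factors adds 30 × (3 + 2 + 1) = 180 terms. On 396 to 500 women that brings back the sparseness it is meant to avoid, so the interactions must be few and chosen in advance.

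**The case against.** The strongest reply is that this is a condensed article. Covariates, interaction terms and the exact form of stratification are usually left to a fuller document, which is not shown. The same paragraph gives moderation analyses a central place, and moderation is the testing of interactions. Pooled models are nowhere ruled out. Stratifying by mode also has a proper use: it shows descriptively whether associations look alike in the two groups. The mode check is not the primary objective.

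Much of this stands and limits the weight of the point. It does not remove it. For mode, the article states a purpose and one method, and that method does not serve the purpose. Moderation is not tied to mode, country or stage.

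A reader might infer several stronger things that the article does not support:

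- **That each country analysis will have about 99 women and 26% power.** The 30-predictor regression appears only as a whole-sample justification, and no text says it will be fitted within a country. The 99 also needs an unstated equal split and the maximal attrition applied to all 660 ("with 660 patients recruited at baseline").
- **That the pooled sample is given up, or that significance will be compared between strata.** The article says neither.
- **That paper users are older or less educated.** This is plausible but not stated. The argument needs only that mode is not assigned.
- **That the count of sites is an error.** The abstract has "five European cancer centers in Italy, Finland, Israel, and Portugal", while a secondary objective is "Examining potential differences in the predictive and outcome variables across the four clinical sites in which the study is conducted". The article places the two Israeli hospitals under one coordinating university and refers to four clinical teams, so four sites fits its own structure. Four groups is also right for stratifying by country.

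**Conclusion.** The point holds for response mode: the stated method cannot answer the stated question, because mode is self-selected and strata alone do not separate its effect from the make-up of the groups. This follows from two statements in the article and needs no numerical assumption. The size and direction of the bias are unknown, since neither the share on paper nor the profile of those women is given.

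For country and stage the point is narrower. Differences should be tested in the pooled sample, because the 85% power belongs to n = 500 as a whole. The per-country figures of 75 to 165 women illustrate this under an assumed equal split and describe no planned analysis. Secondary and supporting analyses are affected directly. The primary objective is touched only through how paper and Noona data are later combined.

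**What to change.** Replace the two stratification sentences with a plan along these lines:

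- **Mode.** Estimate the mode effect on each self-reported outcome in one pooled model with a mode term, adjusted for age, education and either centre or country. Use one of the last two, since centre already determines country. Report the result as an adjusted association, because unmeasured reasons for choosing paper may remain.
- **Country and stage.** Test differences in the pooled sample through main effects and a small, prespecified set of interactions with key predictors. Do not cross all 30 predictors with every factor.
- **Strata.** Show results by mode, country and stage as description only, with the number of women in each.
- **Power.** Say that the stated 85% applies to the whole sample and not to any stratum.

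The cost is a change of wording and a few model terms, with no new data. The downside is a less definite statement about mode, which is all that self-selected mode allows.

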#### Sample Size Considerations

In the context of conventional statistical approaches, such as multiple linear regression, that have typically been employed in the existing relevant literature, a minimal sample size (n=500, considering maximal attrition rates of approximately 40%) is sufficient to ensure 85% power at *P*<.05; this will allow detection of the cumulative contribution of up to 30 independent predictors accounting for as little as 5.3% of total variance of each key study outcome. Furthermore, in a regression model with 30 independent variables, this sample size is sufficient to detect the significant added value of each independent variable, assuming a small effect size (Cohen *f*^2^>0.018). It should be noted, however, that this study proposed, for the first time, the use of nonconventional computational approaches to assess the hypothesized predictive variables. Given the complexity of the data sets and the fact that interactions between parameters are often difficult to specify—a requirement of conventional methods—supervised machine learning methods are emerging as the approach of choice for identifying hidden patterns among predictor variables. Perhaps the most distinct advantage of these methods is their adaptive capacity (ie, their inherent ability to optimize parameter weights based on known individual outcomes). The clinical accuracy of each optimized prediction model will be tested through various cross-validation techniques. 

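### The stated 85% power needs 500 women analysed, but 660 enrolled less the plan's own 40% maximum attrition leaves as few as 396, where power is about 71% (joint) and 76% (single predictor)

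*Protocol article*

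**What the plan says.** In the protocol article, Sample Size Considerations frames its calculation with "In the context of conventional statistical approaches, such as multiple linear regression" and states that "a minimal sample size (n=500, considering maximal attrition rates of approximately 40%) is sufficient to ensure 85% power at" the 5% level. It gives two targets at that size:

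- the "cumulative contribution of up to 30 independent predictors accounting for as little as 5.3% of total variance of each key study outcome";
- in a model with 30 predictors, "this sample size is sufficient to detect the significant added value of each independent variable", with Cohen's f² above 0.018.

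Enrolment is given elsewhere. The Abstract (Methods) plans for 660 women, and Study Participants reports the cohort "with 660 patients recruited at baseline". The article shows no step that links 500, 40% and 660.

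**The concern.** A sample size that takes attrition into account should leave enough women, after the losses, to carry the stated power. Here three figures have to fit together: 500 women for 85% power, losses of up to about 40%, and 660 enrolled. Sixty per cent of 660 is well short of 500.

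The regression statement is the only quantitative support for the sample size in this article. If it does not hold at the attrition it says it considered, the stated detectable effects (5.3% of variance, f² of 0.018) are too favourable for that case. Anyone who later uses those figures to judge what the study could have missed would be working from the wrong sensitivity.

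**Working it through.** **Inputs.** From Sample Size Considerations: n = 500, maximum attrition 40%, alpha 0.05, power 85%, 30 predictors, R² = 0.053 for the joint test, f² = 0.018 for one predictor. From the Abstract and Study Participants: 660 enrolled.

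**Method.** Power of the F test in multiple linear regression from the noncentral F distribution, with noncentrality λ = f² × n and denominator degrees of freedom n − 30 − 1. For the joint test, numerator df = 30 and f² = R²/(1 − R²) = 0.053/0.947 = 0.0560. For one predictor, numerator df = 1 and f² = 0.018.

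**Step 1: reproduce the plan's figure.** At n = 500 the denominator df is 469.

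- Joint: λ = 0.05597 × 500 = 28.0, power 84.4%.
- Single predictor: λ = 0.018 × 500 = 9.0, power 84.9%.

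Reaching 85% exactly takes 507 and 501 women. Two separately stated effect sizes both land on 85% at 500, so 500 is the number analysed and contains no allowance for loss.

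**Step 2: apply the plan's attrition to the plan's enrolment.**

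- 660 × (1 − 0.40) = 396 analysable.
- To keep 500 after 40% loss: 500/0.60 = 833.3, so 834 enrolled.
- Loss at which 660 still leaves 500: 1 − 500/660 = 24.2%.

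**Step 3: power across attrition rates, starting from 660.**

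| Attrition | n analysed | Joint test, R² = 5.3% | One predictor, f² = 0.018 |
|---|---|---|---|
| 20% | 528 | 87.1% | 86.8% |
| 24% | 502 | 84.6% | 85.1% |
| 25% | 495 | 83.9% | 84.6% |
| 30% | 462 | 80.1% | 82.1% |
| 35% | 429 | 75.8% | 79.2% |
| 40% | 396 | 70.9% | 75.9% |

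**Step 4: what 396 can detect with 85% power.** Joint: f² = 0.0725, so R² = 0.0725/1.0725 = 6.8%. One predictor: f² = 0.0228.

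**Step 5: the other reading of 500.** If 500 meant women enrolled, 500 × 0.60 = 300 would be analysed and the stated power would be missed by more. That reading also conflicts with 660 enrolled. It serves only to show that the ambiguous wording does not rescue the sentence.

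**Step 6: other conventions.** Reading 5.3% as f² instead of R² gives 81.6% at 500 and 67.6% at 396. For the single predictor, setting λ = f² × (numerator df + denominator df + 1) gives 82.8% and 72.7%. Both fit the stated 85% less well and give lower power at 396.

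**The case against.** **Forty per cent is a maximum.** This stands. The plan gives no expected rate and does not tie the maximum to a visit. A reader might infer that the study's power is 71% to 76%, or that 396 women are expected at month 18. The article supports neither. The Objectives call for prediction at several time points, and earlier outcomes may keep more women. What remains is that the sentence claims sufficiency with that maximum considered, so it should hold there.

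**The shortfall assumes regression on women with outcome data.** Also fair. The article names no missing-data method, which it may properly leave to a fuller document, and methods using partial follow-up could recover some power. The sample size paragraph does not rely on any such recovery.

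**A one-sided test might rescue the claim.** Sidedness is not stated, and a one-sided test of a single predictor at 396 gives 84.6%, close to 85%. But the same test gives 91.2% at the plan's own 500, so it does not explain the stated figure. It also does nothing for the joint test, which stays at 70.9%.

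**Regression is not the main analysis.** The power claim is confined to conventional methods. The same section then turns to machine learning checked by cross-validation, the study is called a pilot, and Results says recruitment ended in November 2021. This lowers the severity but does not make the figures consistent.

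**More than 30 predictors.** A reader might count the baseline measures in Tables 1 to 3 and infer a further loss of power. The article claims power for up to 30 predictors and nowhere says that all measures enter one model, so that inference is unsupported.

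**Conclusion.** The power statement is wrong as written. With 660 enrolled, the stated power and effect sizes hold only if attrition is at most about 24%, not at the 40% maximum the sentence says it considers. At that maximum, as few as 396 women are analysable. Power is then about 71% for the joint test and 76% for a single predictor, so the chance of missing a joint effect of 5.3% rises from about 16% (100 − 84.4) to about 29% (100 − 70.9).

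This rests on a two-sided or F test at 0.05, regression on women with outcome data, and attrition at its stated maximum. With fewer losses the shortfall shrinks, and below about 24% it disappears.

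The point should be corrected but is not critical. No enrolment decision now depends on it, the main predictive models are judged by other means, and the detectable effects change only modestly.

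**What to change.** Restate the paragraph, with no new enrolment, along these lines:

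> 660 enrolled; as few as 396 analysable if attrition reaches its 40% maximum, giving 85% power to detect R² of about 6.8% with 30 predictors and f² of about 0.023 for a single predictor. The 5.3% and 0.018 figures hold only if attrition does not exceed about 24%.

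The cost is one reworded paragraph and slightly less favourable stated detectable effects: R² moves from 5.3% to about 6.8%, and f² from 0.018 to about 0.023.

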### Data Collection Storage and Security

The multicenter pilot study involves the collection of personal data. Therefore, issues regarding confidentiality, privacy, and protection of data have been addressed so as to be compliant with Regulation (EU) 2016/679 of the European Parliament and of the Council of 27 April 2016 on the protection of natural persons with regard to the processing of personal data and on the free movement of such data, and repealing Directive 95/46/EC (General Data Protection Regulation). All data collected through the questionnaires and all relevant information about participants are stored in Noona electronic databases. The data are processed using a coding system that allows for the identification of patient identity only if and when necessary for the scientific objectives of the research project.

The lists below reflect the partners involved in the project and their respective roles regarding data collection, storage, and security.

Clinical partners are as follows:

IEO: promoter of the multicenter pilot study and data controllerHUS: coordinator of the EU BOUNCE project and data processorRabin Medical Center and the Shaare Zedek Medical Center, under HUJI: data processorCHAMP: data processor.

Technical partners are as follows:

FORTH: data analysis and storageICCS: data analysisSingularLogic: data analysis and model developmentNordic Healthcare Group: model developmentNoona: data storage.

